## 4.4 Outcomes

### Primary outcome:

The primary outcome of this study will be the difference of the mean proportion of adequately reported items of the 10 most important and poorly reported CONSORT items between the two intervention arms.

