#### 4.8.2 Data analysis

All quantitative variables will be described using means and standard deviations, or median and interquartile ranges in case severe departures from a normal distribution are identified. Data distribution will be inspected visually (i.e. by histograms) instead of performing formal statistical tests for normality. Categorical variables will be described using frequencies and percentages. For the primary and secondary outcomes, we will estimate the difference between means between the two groups and report them with respective 95% confidence intervals.

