#### 4.8.3 Analysis of primary endpoint

The primary outcome will be the difference of the mean proportion of adequately reported items of the 10 most important and poorly reported CONSORT items. If the data on the primary outcome is normally distributed then the two groups (i.e. C-short plus usual practice vs. usual practice) will be compared using an unpaired Student's t-test to compare the unadjusted mean proportion of adequate reporting. If the data is not normally distributed, comparisons will be performed using a non-parametric equivalent test (i.e. Wilcoxon-Mann-Whitney test for testing whether the population medians of the two groups are the same).

For the analyses of the primary outcomes a p-value of 0.05 (5% significance level) will be used to indicate statistical significance and treatment effect (mean difference) reported with 95% confidence intervals (or median and respective interquartile ranges, in case of asymmetric distribution). Exact p-values will be presented up to three decimal places. We anticipate there will be no missing data in this study, neither at the individual C-short items, nor at the manuscript level. This is due to the study design, which will include only the randomised manuscripts that are accepted for publication.

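### The primary test and the reported effect depend on how normal the data look, although the outcome is defined, and the trial sized, as a difference in means

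*Protocol*

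**What the plan says.** Section 4.4 of the protocol defines the outcome in terms of means: "The primary outcome of this study will be the difference of the mean proportion of adequately reported items", taken over ten CONSORT items and compared between arms. Section 4.6 bases the sample size on a two-sided t-test. Section 4.8.2 says that normality will be judged by eye from histograms. It also states, for primary and secondary outcomes and without condition, "we will estimate the difference between means between the two groups and report them with respective 95% confidence intervals".

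Section 4.8.3 is conditional. If the data are normal, the arms are "compared using an unpaired Student's t-test to compare the unadjusted mean proportion of adequate reporting". Otherwise, "If the data is not normally distributed, comparisons will be performed using a non-parametric equivalent test", namely the "Wilcoxon-Mann-Whitney test for testing whether the population medians of the two groups are the same". The treatment effect is to be the mean difference with a 95% confidence interval, "or median and respective interquartile ranges, in case of asymmetric distribution".

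Section 4.8.4 promises mean differences with 95% intervals for the secondary outcomes and applies the same switch of test to the continuous ones.

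**The concern.** Three things are at issue.

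- **The quantity reported can change.** A median and interquartile range describe one arm. They are neither a between-arm effect nor a confidence interval, and they do not estimate the outcome defined in section 4.4.
- **The trigger is a visual judgement of the trial's own outcome data,** with no stated criterion. Both tests are named in advance, but which one becomes primary is settled only after the data are seen.
- **The property claimed for the fallback is wrong.** Wilcoxon-Mann-Whitney tests equality of medians only under restrictive conditions, such as a pure location shift between arms. A score that piles up at a ceiling of 1.0 does not meet them.

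At stake is whether the report gives an estimate with an interval for the outcome that the trial was designed to measure.

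**Working it through.** **1. The plan's own sample sizes.** Inputs from section 4.6: SD 0.25, two-sided 5%; scenario 1 is 0.56 versus 0.70 at 90% power, scenario 2 is 0.71 versus 0.82 at 80% power. Formula: n per arm = 2(z₁₋α/₂ + z₁₋β)² SD² / δ².

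- Scenario 1: 2 × (1.960 + 1.282)² × 0.0625 / 0.14² = 67.0, so 68. The noncentral t solution is 67.99, so 68. Power at 68 is 0.900.
- Scenario 2: 2 × (1.960 + 0.842)² × 0.0625 / 0.11² = 81.1, so 82. The noncentral t solution is 82.05, so 83. Power at 83 is 0.805.

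Both stated figures (68 and 83) are reproduced. They are for a t-test on a difference in means.

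**2. Can the score look normal in scenario 2?** The score cannot exceed 1.0. Distance of the ceiling from the mean:

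- Control: (1 − 0.71) / 0.25 = 1.16 SD. A normal curve would put 12% of articles above 100%.
- C-short: (1 − 0.82) / 0.25 = 0.72 SD. A normal curve would put 24% above 100%.

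How skewed the scores are depends on an assumed shape. Three were tried:

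| Assumed shape | Skewness, control / C-short | At 10 of 10, control / C-short |
|---|---|---|
| Beta-binomial, SD 0.25 | −0.73 / −1.47 | 20% / 48% |
| Normal rounded and clipped to 0–1, SD 0.25 | −0.62 / −1.40 | 24% / 52% |
| Table 3 item rates, Gaussian copula, item correlation 0.4 (SD 0.22 / 0.18) | −0.7 / −1.2 | 13% / 29% |
| Same, item correlation 0.2 | −0.5 / −0.9 | 7% / 21% |

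The copula rows also assume a common logit shift for the C-short arm. The C-short arm is left-skewed in every row. In scenario 1 (beta-binomial, SD 0.25) skewness is milder: −0.17 and −0.68.

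**3. Is the switch needed?** With 83 per arm and 10,000 simulated trials per setting, on the first two shapes with SD 0.25 or 0.23:

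- The t-test's type I error is 4.9% to 5.2%.
- Coverage of the 95% interval for the mean difference is 94.8% to 95.2%.
- Power at 0.71 versus 0.82 with SD 0.25 is 0.80 to 0.81.
- Expected half-width of the interval is 1.97 × 0.25 × √(2/83) = 0.077.

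The planned analysis therefore works on skewed scores of this kind.

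**4. What does the switch change?** At 0.71 versus 0.82, t-test and Wilcoxon power are:

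- first two shapes, SD 0.25: 0.80–0.81 against 0.93–0.95, with disagreement on significance in 12–15% of trials;
- copula, correlation 0.4: 0.93 against 0.94, with disagreement in 3%.

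The descriptive contrast moves too. With the same means and SD, the arm medians are 0.8 and 0.9 under the beta-binomial but 0.7 and 1.0 under the clipped normal. The gap between medians is 0.1 or 0.3 while the mean difference is 0.11 in both.

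**5. Does the rank test test medians?** A constructed example on the 0–1 scale has both population medians at 0.8 and means of 0.684 and 0.826. Wilcoxon-Mann-Whitney rejected in 97.3% of 4,000 simulated trials. It was responding to a real difference between the distributions, but not to a difference in medians.

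**The case against.** The strongest reply is that section 4.8.2 promises the mean difference with a 95% interval whatever the distribution, so the estimate is not lost. A reader might infer from section 4.8.3 that the trial would report no interval for its primary outcome. The protocol does not establish that: one parenthesis in 4.8.3 conflicts with an unconditional sentence in 4.8.2. Nor does section 4.4 promise an interval; it only names the difference of means. This part of the reply stands, and the point is a conflict to be reconciled.

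A reader might also infer that the fallback will almost certainly become the primary analysis. That is too strong. The SD of 0.25 is deliberately larger than the 0.23 of the previous study, the shape is assumed, and the judgement is visual. For choosing descriptive summaries, section 4.8.2 requires a severe departure from normality. At an assumed SD of 0.15, control-arm skewness is only −0.1 to −0.3.

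Nor is there material error-rate harm. Each test holds about 5% under the null. Even a free choice of the smaller p-value, which the protocol does not allow, would give only 5.7% to 6.8% at SD 0.23 to 0.25. Wilcoxon is no less powerful in the SD 0.25 and copula-0.4 settings above, and its large advantage there depends on the assumed shape. The equal-medians example is constructed and has a true mean difference of 0.14. It shows that the description is wrong, not that the trial would reach a wrong conclusion.

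What remains is the conflict over what is reported, a primary test that depends on the data's appearance, and a mistaken description of the fallback.

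**Conclusion.** The point holds in this form. Section 4.8.3 lets a visual judgement change the primary test and, if the data are asymmetric, replace the mean difference and its interval with medians and interquartile ranges. That conflicts with the outcome in section 4.4, the t-test sample size in section 4.6 and the unconditional statement in section 4.8.2. The statement that the fallback is "testing whether the population medians of the two groups are the same" is wrong for a capped score.

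Under scenario 2, which sets the final sample size, left skew is to be expected, so the switch is plausible. No probability can be put on it. The conclusion that the switch is unnecessary rests on the protocol's means and SD with assumed score shapes. The damage is to the estimand, its interval and the reading of the result. Sample size, power and type I error are not in question.

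**What to change.** In section 4.8.3, state that the primary analysis is the difference in mean proportions with a 95% confidence interval and a t-based test (for example Welch), whatever the distribution. Make Wilcoxon-Mann-Whitney a sensitivity analysis, delete the statement that it compares medians, and delete the median and interquartile range as an alternative form of the treatment effect. They can remain as descriptive summaries per arm. This brings section 4.8.3 into line with 4.4, 4.6 and 4.8.2.

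Apply the same rule to the score-type secondary outcomes. Section 4.8.4 already promises their mean differences with intervals, so only the switch of test needs to change.

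The cost is wording: no extra articles, and 83 per arm stands. The downside is that the rank test may be somewhat more powerful under strong ceiling effects, and that gain is given up in the primary analysis.

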#### 4.8.4 Analysis of secondary endpoints

To investigate the effect of the intervention on the secondary outcomes, mean differences with respective 95% confidence intervals will also be reported for these outcomes. If normality is not observed for any of the continuous secondary outcomes, the same strategy adopted for the primary outcome (use of a non-parametric equivalent to the Student's *t*-test) will be used.

A p-value of 0.05 will indicate statistical significance for the observed treatment effect on the secondary outcomes. Exact p-values will be presented up to three decimal places. Similarly to the primary outcome, we anticipate there will be no missing data for any of the secondary outcomes, as we will have access to the Editorial Management system of the included journals, where all relevant information is automatically reported.

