### Secondary outcomes:

Secondary outcomes will include the following:

- Mean proportion of adequate reporting of the 10 most important and poorly reported CONSORT items, considering each sub-item (see also “Assessment of outcomes”) as a separate item.
- Mean proportion for each of the 10 most important and poorly reported CONSORT items separately (including also separate analysis of sub-items).
- Time from assigning an academic editor until the first decision (as communicated to the author after the first round of peer-review).
- Proportion of articles directly rejected after the first round of peer-review.
- Proportion of articles published.

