### Data collection methods:

The outcomes will be assessed independently by two (blinded or at least partially blinded; see “blinding”) outcome assessors with expertise in the design and reporting of clinical trials. Any disagreement will be resolved by consensus or if necessary by consulting a third assessor. To ensure consistency between reviewers, we will first pilot the data extraction form; any disparities in the interpretation will be discussed and the data extraction form will be modified accordingly.

Adequate reporting of items will be assessed from published full-text publications adhering to the CONSORT C-short checklist (21). The following included items have sub-items which will be extracted separately:

- Outcomes (item 6a): (i) Define primary outcome, (ii) how it was measured, (iii) at what time point, and (iv) the analysis metric (e.g. change from baseline, final value).
- Sample size (item 7a): (i) The estimated outcomes in each group, (ii) the  $\alpha$  (type I) error level, (iii) the statistical power (or the  $\beta$  (type II) error level), (iv) for continuous outcomes, the standard deviation of the measurements
- Blinding (item 11a): Is the blinding status clear for the following persons: (i) Healthcare provider, (ii) patients, and (iii) outcome assessors.
- Funding (item 25): (i) The funding source, and (ii) the role of funder in the design, conduct, analysis, and reporting.

All items will be judged as either “yes” meaning adequately reported, “no” meaning not adequately reported, or “NA” meaning that this sub-item is not applicable for this RCT. Items with different sub-items will only be judged as adequately reported if all relevant sub-items were adequately reported.

- Time from assigning an academic editor until the first decision: The day when the academic editor was assigned and the day of the first decision (e.g. major revision, minor revision, rejected) will be extracted to calculate the number of days until the first decision.
- Proportion of articles directly rejected after the first round of peer-review: Articles which were not invited for re-submission will be labelled and counted.
- Proportion of articles published: Articles which will be published will be counted and collected for data extraction.

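### Section 4.8.4 makes p = 0.05 the mark of a significant effect for 26 to 28 secondary comparisons, with no hierarchy or exploratory label, so one or more chance findings is more likely than not

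*Protocol*

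**What the plan says.** For the primary outcome, section 4.8.3 states: "For the analyses of the primary outcomes a p-value of 0.05 (5% significance level) will be used to indicate statistical significance". Section 4.8.4 sets the same threshold for the secondary outcomes: "A p-value of 0.05 will indicate statistical significance for the observed treatment effect on the secondary outcomes". Sections 4.8.2 and 4.8.4 also require differences with 95% confidence intervals, and 4.8.4 asks for exact p-values.

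Section 4.4 lists five secondary outcomes, two of which are built from the checklist. One is a composite score "considering each sub-item (see also “Assessment of outcomes”) as a separate item". The other is "Mean proportion for each of the 10 most important and poorly reported CONSORT items separately (including also separate analysis of sub-items").

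The data collection text in section 4.4 defines the sub-items:
- item 6a has four: "i) Define primary outcome, (ii) how it was measured, (iii) at what time point, and (iv) the analysis metric";
- item 7a has four, the last being "iv) for continuous outcomes, the standard deviation of the measurements";
- item 11a has three: "i) Healthcare provider, (ii) patients, and (iii) outcome assessors";
- item 25 has two: "i) The funding source, and (ii) the role of funder in the design, conduct, analysis, and reporting".

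The remaining secondary outcomes are time to first decision, direct rejection after the first review round, and publication. Section 4.8.1 calculates all outcomes in randomised manuscripts accepted for publication, and analyses time to first decision a second time in all randomised manuscripts.

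Section 4.8.5 describes the subgroup displays as exploratory and not conclusive. No such description is attached to the secondary outcomes.

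**The concern.** The protocol states a decision rule: a secondary result at 0.05 counts as a significant treatment effect. The rule covers a long list of item and sub-item comparisons. It sets no order among them and does not tie them to the primary result. Because the subgroup section carries an exploratory caveat and the secondary section does not, a reader would take the secondary results as having the same evidential standing as the primary one.

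At stake is what the trial may claim. Item-level results will naturally be read as showing which parts of CONSORT reviewers can improve. If the primary difference were null, the rule as written would still permit an individual item or sub-item to be reported as a significant effect, and with this many comparisons chance alone would often supply one.

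**Working it through.** **Plan's own figure.** The protocol gives no familywise error rate, so there is none to reproduce. Its sample size does reproduce and supplies the n used below. For 71% versus 82%, SD 0.25, two-sided 5% and 80% power, n per arm = 2 × (1.960 + 0.842)² × 0.25² / 0.11² = 81.1, so 82. The t-test version gives 82.05, so 83, with 80.5% power.

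**Count of comparisons** (sections 4.4 and 4.8.1)

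| Set | Number |
|---|---|
| Sub-item composite | 1 |
| Items | 10 |
| Sub-items (4 + 4 + 3 + 2) | 13 |
| Time to first decision, two populations | 2 |
| Direct rejection | 1 |
| Publication | 1 |
| Total | 28 |

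Read literally, section 4.8.1 evaluates rejection and publication only in accepted manuscripts, where they are constants (0% and 100%). That leaves 26 testable comparisons.

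**Expected false positives with no true effect.** 28 × 0.05 = 1.4; 26 × 0.05 = 1.3. Correlation does not alter these expectations.

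**Chance of at least one, independence.** 1 − 0.95²⁸ = 76.2%; 1 − 0.95²⁶ = 73.6%; for the ten items, 1 − 0.95¹⁰ = 40.1%. This is a reference value only, because the comparisons are correlated.

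**How correlated are the items?** The protocol's SD and Table 3 rates give an average. If the ten items were independent, the sum of p(1 − p) over the Scenario 1 rates would be 2.020, so the SD of the mean proportion would be √2.020 / 10 = 0.142. The SD in the earlier study was 0.23, so the variance of the item count is 100 × 0.23² = 5.29. Average covariance over the 90 ordered item pairs = (5.29 − 2.020) / 90 = 0.0363. The average product of two item SDs is 0.200. Implied correlation = 0.0363 / 0.200 = 0.18. With the planning SD of 0.25 it is 0.23. With the Scenario 2 rates it is 0.24 (SD 0.23) to 0.31 (SD 0.25).

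**Chance of at least one, equally correlated normal test statistics**

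| Correlation | 28 | 26 | Ten items |
|---|---|---|---|
| 0 | 76% | 74% | 40% |
| 0.2 | 70% | 68% | 38% |
| 0.3 | 64% | 62% | not run |
| 0.5 | 49% | 47% | 29% |
| 0.7 | 33% | 32% | not run |

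**Chance of at least one, simulated data.** This used 83 per arm, binary items at the Table 3 rates, sub-items nested so that an item is adequate only if all its sub-items are, t-tests at 0.05, and 2,000 replicates per setting. The protocol does not give the correlations among sub-items, or the shares of manuscripts rejected (30%) and published (50%), so these are assumptions.
- Moderate correlation (latent 0.3 to 0.4 between items, 0.31 to 0.8 within an item): 64% to 68% for 28; 60% to 65% for 26.
- Strong correlation (0.6 between, 0.9 within): 57% to 58% for 28; 53% for 26.
- Ten items alone, over all settings: 31% to 39%.
- Mean number of false positives: 1.30 to 1.39.

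**The case against.** The strongest reply is that the trial has one objective, one primary outcome and one primary test, and the sample size rests on that test. Nominal p-values for outcomes labelled secondary are common, and multiplicity is often left to a statistical analysis plan, which is not shown here. Estimates, intervals and exact p-values will be reported and the anonymised dataset released, so a reader can apply a correction.

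Much of this stands. The confirmatory claim is protected, and leaving secondary outcomes unadjusted is defensible. But the protocol is not merely silent. It says what a secondary p-value of 0.05 will indicate, and an analysis plan that treated these results as exploratory would have to qualify that sentence.

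The size can also be challenged, and in part rightly. Independence is impossible: four items are functions of their sub-items, the composite uses the same data, and the two time analyses overlap. Items near ceiling also reject less often than 5%: with 83 per arm and assumed true rates of 95%, 98% and 99%, the t-test rejects 4.2%, 3.3% and 0.9% of the time. So 76% should not be the headline. For the ten items alone the chance stays below even odds.

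A reader might infer more than the text supports:
- that every secondary comparison will be declared significant, whereas each is only judged against 0.05;
- that the protocol rules out adjustment, or says secondary claims stand after a null primary result, whereas it states no condition either way;
- that the primary conclusion is at risk, whereas its single test is untouched.

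**Conclusion.** The point holds as a fault in a stated rule. Across 26 to 28 comparisons, a checklist with no effect would be more likely than not to produce at least one result that section 4.8.4 calls significant.

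The range of roughly 55% to 75% assumes that all secondary nulls are true and that correlation runs from none to strong. The lowest simulated value, for 26 comparisons under strong correlation, is 53%. The chance falls below one half only if all the statistics correlate at about 0.5 or more, which is above the 0.18 to 0.31 average implied between items by the protocol's own SD and rates.

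This limits what may be claimed for individual items and sub-items. It shows no error in a stated figure, and it does not establish that formal adjustment is obligatory. It is a cheap improvement to make before the results are known.

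**What to change.** Replace the significance sentence in section 4.8.4 with text such as: *Only the primary outcome carries a claim of statistical significance at the 5% level. Results for the items, the sub-items and the sub-item composite are reported as differences with 95% confidence intervals, not adjusted for multiplicity, and are exploratory.*

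Time to first decision, rejection and publication may keep nominal p-values. They track possible unwanted effects on the editorial process, where strict error control is not clearly desirable.

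If item-level claims are wanted, an optional addition is Holm's procedure across the ten items, applied only after a significant primary result.

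The change needs no new data, no larger sample and no new analysis. The sponsor gives up calling individual items or sub-items significant at an unadjusted 0.05. The relabelling does not change how often an unadjusted interval excludes zero by chance. It changes what may be concluded when one does, so the words on multiplicity should stay with the intervals wherever they are reported.

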#### 4.6. Sample size

For the sample size calculation we hypothesise in a first scenario (Table 3) that the intervention C-Short will result in a 25% relative increase in adequate reporting compared to the control (meaning that 70% of items will be adequately reported in the intervention group and 56% in the control group). This is based on the rate of reporting of the 10 most important and poorly reported items was 0.56 (meaning that a mean of 56% of the 10 most important and poorly reported items were reported) in the control group of a previous study called WebCONSORT (38). The standard deviation (SD) in the same study was 0.23. However, we calculated our sample size to account for a slightly bigger variability in our data ( $SD = 0.25$ ). To demonstrate a significant difference with a power of 90% and a type 1 error at 5% a total of 136 articles will be required in this scenario (68 per treatment arm; based on a two sided t-test).

The staff from one journal which will most likely be included (i.e. *PLoS One*) pointed out that 3 out of the 10 assessed items (i.e. item “Registration”, “Protocol”, and “Funding”) should always be implemented given their template. Assuming that this journal will recruit a high proportion, and that also other journals might update their templates, we increased the sample size in a second scenario, in which all these 3 items would have an overall adherence of 90% in the control arm (Table 3). This would entail an overall baseline adherence with the 10 CONSORT-short items of 71%. Based on a two sided t-test, a sample size of 166 (83 per treatment arm) will have a power of 80% to find a 15% relative increase (71% adherence in control group; 82% adherence in intervention group;  $SD = 0.25$ ; a type 1 error at 5%).

Since the final sample size will be based on the number of articles published, rather than on the number of manuscripts randomised, eligible RCTs will be included and randomised until the number of 83 published RCTs is reached in each arm (resulting in no less than 166 articles), to avoid loss of power due to potential imbalance between arms. Recruitment will be stopped as soon as both arms reach the sample size of 83. After recruitment stop we will wait three month so that manuscripts which are still in production can be published. Manuscripts which are published after the three month period will be excluded.

**Table 3:** Assumptions for sample size calculations in two different scenarios.

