#### 4.7 Data management and confidentiality

Outcomes from publications will be assessed and extracted in duplicate. Since this information is not confidential, we will use Google Forms for data extraction from published RCTs. Data entered will be validated for completeness.

Data from the editorial manager software (e.g. Title of manuscript, first author, randomisation ID, Journal, date when manuscript was accepted by and academic editor, date when the final decision was made, final decision, number of peer-reviewers who peer reviewed the manuscript, the peer review) will be extracted, anonymised and entered in a password protected database which is saved on a server from the University of Oxford. Data will be managed and curated according to University of Oxford regulations, which includes regular back-up (on a daily basis) of the virtual drives where the data are stored.

The raw data extracted from the included manuscripts can be made openly accessible in an anonymised way (i.e. giving the included RCT a number instead of identifying them). Derived/aggregated data, including anonymised information generated from the journals' editorial manager software, will be stored and made available to the research community when the project ends (see also "8. Publication policy and access to data"). Where appropriate, the researcher who has access to the editorial manager software (BS) and anyone else who will see the identifiable data will sign a confidentiality agreement with the participating journals, confirming that they will not share identifiable data with any other party. Journals such as the BMJ series state in their Company Privacy Statement that research programmes for quality improvement might be in place. Furthermore, peer reviewers for all BMJ journals receive the following statement in their invitation letter *"We are constantly trying to find ways of improving the peer review system and have an ongoing programme of research. If you do not wish your review entered into a study please let us know by emailing [...] as soon as possible."*

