## 4.8 Statistical methods

### 4.8.1 Populations of analysis

The main population for analysis will be all manuscripts randomised and accepted for publication in the participating journals. Differently from RCTs conducted with patients, where drop outs need to be carefully considered (e.g. multiple imputation of missing data), we are only interested in the reporting adherence of RCTs that are published. All outcomes will be calculated based on the main population for analysis. The secondary outcome "Time to the first decision", will additionally be calculated considering all randomised manuscripts (including the ones which were not published).

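### The no-missing-data premise does not hold for the additional all-randomised analysis of time to first decision, where undecided or withdrawn manuscripts may have no value

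*Protocol*

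**What the plan says.** Protocol 4.8.4 compares the secondary outcomes by mean differences with 95% confidence intervals, with a non-parametric test for continuous outcomes that are not normal. It says "we anticipate there will be no missing data for any of the secondary outcomes", and gives as the reason "as we will have access to the Editorial Management system of the included journals, where all relevant information is automatically reported".

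Section 4.8.3 makes the same assumption for the primary outcome on a different ground: the design, "which will include only the randomised manuscripts that are accepted for publication".

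Section 4.8.1 sets the populations. The general rule is "All outcomes will be calculated based on the main population for analysis", meaning randomised manuscripts accepted for publication. Time to first decision is the exception: it "will additionally be calculated considering all randomised manuscripts (including the ones which were not published").

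Section 4.6 randomises manuscripts until 83 per arm are published, and then: "After recruitment stop we will wait three month so that manuscripts which are still in production can be published".

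Under Data collection methods in 4.4, time to first decision runs from assignment of the academic editor to the first decision. Direct rejection after the first round is put into practice as: "Articles which were not invited for re-submission will be labelled and counted".

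**The concern.** The ground given for the primary outcome works: every accepted paper has been published or is on its way there, and has had a first decision. That ground disappears once all randomised manuscripts are analysed. The ground given in 4.8.4, access to the editorial system, guarantees that a recorded date can be read. It does not guarantee that there is a date.

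What is at stake is the reading of delay. Time to first decision is the protocol's direct measure of whether C-short slows review. The all-randomised version is the one comparison of delay that does not condition on acceptance, which happens after randomisation. If undecided manuscripts are left out, the longest times go, and more of them go from a slower arm. A real delay would then tend to look smaller than it is.

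**Working it through.** **What the protocol supplies.** It gives no distribution of decision times, accrual period, withdrawal rate or expected delay, so there is no figure of its own to reproduce for this outcome. Its sample sizes concern the primary outcome only. They do reproduce: a two-sided t-test with difference 0.14, SD 0.25 and 90% power gives 68 per arm; difference 0.11, SD 0.25 and 80% power gives 82.05, rounded up to 83.

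**Where missing values arise.**
- Accepted manuscripts: a first decision always exists, so none are missing.
- All randomised manuscripts: randomisation occurs when the first reviewer accepts and continues up to the recruitment stop. A late entrant may still be under review at data close. A manuscript withdrawn before a decision has no date at any time.

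**Size, on assumptions.** Take uniform entry over A days, data close w = 90 days after the stop (the three-month wait used as a stand-in), and lognormal time T from randomisation with median exp(μ) and log-SD σ. Only decided manuscripts are analysed. Then

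- F(u) = Φ((ln u − μ)/σ)
- undecided share = 1 − (1/A) ∫ F(u) du, over u from w to w + A
- true mean = exp(μ + σ²/2); for example 60 × exp(0.18) = 71.8 days
- observed mean = ∫ E[T; T ≤ u] du / ∫ F(u) du over the same range, where E[T; T ≤ u] = exp(μ + σ²/2) Φ((ln u − μ)/σ − σ)

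With C-short 15% slower (differences taken before rounding):

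| Accrual | Control median | σ | Undecided, control / C-short | True delay (days) | Observed delay (days) | Shortfall |
|---|---|---|---|---|---|---|
| 18 months | 45 | 0.5 | 0.4% / 0.7% | 7.7 | 7.4 | 4% |
| 18 months | 60 | 0.6 | 2.1% / 3.1% | 10.8 | 9.5 | 12% |
| 18 months | 90 | 0.6 | 6.1% / 8.4% | 16.2 | 12.7 | 21% |
| 12 months | 60 | 0.6 | 3.1% / 4.6% | 10.8 | 8.8 | 18% |
| 12 months | 90 | 0.6 | 9.0% / 12.3% | 16.2 | 11.2 | 31% |

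With a fixed 10-day delay instead (medians 45 to 90 days, σ 0.5 to 0.7, accrual 180 to 540 days), the observed difference runs from about 9.9 days (1% short; 540 days, median 45, σ 0.5) to about 8.0 days (20% short; 180 days, median 90, σ 0.7). Withdrawal unrelated to decision time, about 3% by the median time in each arm, leaves this range almost unchanged, although up to 22% of control and 25% of C-short manuscripts then have no date.

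The 31% is not a ceiling. Proportional slowing with only six months' accrual (180 days, median 90, σ 0.6) gives 16.2 days seen as 7.9, about 51% short.

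**Against sampling error.** In the 12-month, median-60 case the bias is 10.8 − 8.8 ≈ 2 days. With observed SDs of 40.8 and 45.1 days and an assumed 125 manuscripts per arm, the standard error is √((40.8² + 45.1²)/125) ≈ 5.4 days.

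**Rejection wording.** Read literally, not being invited to resubmit also describes a withdrawn paper. If withdrawals were counted as rejections, with an equal rejection rate r among decided papers and withdrawal of 2% in control and 5% in C-short (all assumed), the false difference is (1 − r) × (0.05 − 0.02): 2.4 points at r = 0.2 and 1.8 points at r = 0.4. Equal withdrawal gives none.

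**The case against.** Several stronger readings are tempting, and the protocol does not support them.

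- *The whole outcome is compromised.* It is not. The main analysis is in accepted manuscripts, where the premise holds. Only the additional analysis is affected.
- *Data close three months after recruitment stops.* Section 4.6 sets that wait for papers in production to be published. It is not stated as the cut-off for first-decision dates. A later cut-off would leave fewer undecided manuscripts.
- *Any delay is bound to be understated.* That tendency follows for undecided manuscripts if they are dropped. The protocol never mentions withdrawal, and withdrawals could bias either way depending on which papers are withdrawn.
- *Only means are compared.* There is a rank-test fallback, though in its ordinary form it does not handle censoring either.
- *Withdrawn papers will be reported as rejected.* The outcome is named as rejection after the first round of review, which arguably excludes a paper withdrawn or undecided before that round ends, and an accepted paper is plainly not rejected. This is loose wording.
- *The first-decision date will not be collected.* Section 4.7 on data management does list "date when the final decision was made, final decision, number of peer-reviewers who peer reviewed the manuscript", but as examples. Section 4.4 already requires the day of the first decision, from the editorial software. No fault lies there.

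It can also be said that an expectation of no missing data is not a complete-case rule, and that handling of missing values is commonly left to the SAP. That is fair, and the lack of a detailed rule is not the complaint. What stands is that the protocol states a premise which its own all-randomised analysis contradicts, and names methods that depend on it.

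Finally, the sizes rest on assumed inputs and start the clock at randomisation rather than at editor assignment. With an assumed 14-day lag, the undecided shares in the 12-month, median-60 case fall to 2.3% and 3.5%, while the shortfall barely changes. A bias of about 2 days is also modest beside a standard error of 5.4. Both points temper the size but do not rescue the premise.

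**Conclusion.** The point holds for one analysis: time to first decision in all randomised manuscripts. There the no-missing-data premise does not follow, and neither planned comparison can use a manuscript without a decision date. Dropping undecided manuscripts tends to shrink a real delay. The shortfall is about 1% to 31% across the main settings (medians 45 to 90 days, a 90-day wait, and either a 10-day or a 15% delay), negligible with fast decisions and long accrual, and larger still with short accrual and proportional slowing. These are illustrations, since the protocol supplies none of the inputs. The direction of any bias from withdrawals is unknown. The primary outcome, the sample size and the accepted-manuscript analysis are not touched. The definition of direct rejection needs only a clarification.

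**What to change.** In 4.8.4, remove the no-missing-data premise for the all-randomised analysis of time to first decision and state the date on which first-decision data are closed. Analyse all randomised manuscripts as time-to-event data: undecided manuscripts censored at data close, withdrawal before a first decision treated as a competing event, and results given as medians or a restricted mean difference with 95% CI.

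In 4.4, define direct rejection as a recorded first decision of reject, and report withdrawn and undecided manuscripts separately by arm. This makes sense only with all randomised manuscripts as the denominator. Section 4.8.1 as written would compute rejection among accepted papers, where it is zero by construction, so the two sections should be reconciled.

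The cost is wording and one standard analysis. First-decision dates are already to be extracted from the editorial software; the status and date of any withdrawal would be added from the same source. The small downside is that a restricted mean or median replaces a plain mean difference in days for this analysis.
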